**IMAGE 1 fig1:**
[figure not shown]
Sample size for frequency in the military pilot’s population using OpenEpi.

#### Recruitment and screening

3.2.2

The collaboration between Évora University and the PA involved reaching out to the Head of the Chief of Staff Cabinet. Under this collaborative protocol, a Ph.D. student will administer a yoga intervention at the chosen airbase 11 in Beja, while a team from Évora University conducts on-site baseline and post-intervention data collection. The authorization for this collaborative effort was granted by the Portuguese Air Force’s Head of the Chief of Staff Cabinet.

Pilots will undergo a comprehensive briefing on the study’s general parameters and will be extended a voluntary invitation to participate. Following this briefing, participants will be required to sign an informed consent form in adherence to the Helsinki Declaration. Any queries or concerns can be addressed during this stage to ensure clarity and compliance with ethical standards.

#### Randomization procedure and blinding

3.2.3

Upon inclusion, volunteers will be allocated to either a waiting list (control group) or a yoga class (intervention group) through a computer-based algorithm (random.org), to be facilitated by the team captain of the pilots. All study personnel, excluding the team captain and one study coordinator from Évora University, will be kept unaware of the group allocation. Participants will be explicitly instructed to refrain from disclosing their group assignment to the study team. To uphold impartiality, all data will be coded for subsequent processing and analysis, maintaining blindness to group allocation. The final coded trial dataset will be made available to all team members for analysis.

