#### Sample size determination

3.2.1

Among all military personnel in the Portuguese Air Force, the inclusion criteria for participation in this study comprise healthy individuals serving as military pilots actively engaged in their training (tirocinium) at the PAA, which consists of taking the course titled “Masters in Military Aeronautics: Aviator Pilot Specialist.”

Conversely, the exclusion criteria encompass military pilots on active duty either preceding (not aviation pilots yet) or following the tirocinium (distributed by different airbases inside and outside the country and flying different types of aircrafts in restricted, classified or warzones), those with injuries, and individuals undergoing sudden lifestyle changes (e.g., initiating or discontinuing smoking habits, commencing, or ceasing any form of medication, or adopting a new diet).

There are currently 19 pilots actively undergoing their training (tirocinium) at the PAA, serving within “Esquadra 101 - RONCOS,” situated at Airbase 11 in Beja, which comprises the totality of this population for the PA. These pilots are divided into two classes, and they share common aircrafts, specifically the Aerospatiale Epsilon TB-30. Additionally, both classes are assigned comparable workloads and operational tasks.

Within these criteria there are 19 individuals serving as military pilots actively engaged in their training (tirocinium) at the PAA, specifically within the PA course titled “Masters in Military Aeronautics: Aviator Pilot Specialist,” and our sample size is calculated with OpenEpi, with a 95% confidence interval, which corresponds to 19 subjects—the totality of this population, as seen in Image 1.

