#### Study flow

3.3.1

The study team will visit Airbase 5 in Monte Real to consult with the F16 Team Captain. The objectives include planning and scheduling visits, testing the proposed protocol, assessing all pertinent equipment, identifying, and rectifying potential errors before the initiation of the initial data collection. During this meeting, interviews with the Team Captain will be conducted to evaluate the perceived needs of pilots during their aircraft piloting duties. The insights obtained, combined with findings from the literature, will guide the tailoring of the yoga intervention.

A baseline data collection session will be organized in Airbase 11 in Beja, with study participants selected randomly based on availability and location undergoing evaluation over two consecutive days during pilots’ work hours from 8:30 to 19:00. Oversight of the data collection will be provided by experts in Sports Exercise and Health from Évora University, the study coordinator, and a simulator controller from the Air Force team.

The yoga group will integrate a one-hour yoga class into their work schedule, in Airbase 11 in Beja, twice a week for a 12-week period. For those on missions with conflicting schedules, alternative days and times will be accommodated. Each pilot is required to complete 24 yoga classes within the designated 12 weeks. The yoga intervention, led by the study coordinator—an Ashtanga Vinyasa Yoga expert with over 300 h of training and approximately 10 years of teaching experience—will be conducted.

Post-intervention data collection will follow the completion of the yoga program, with study participants, randomly divided based on availability and location, undergoing evaluation over two consecutive days, in Airbase 11 in Beja, during pilots’ work hours from 8:30 to 19:00. Supervision will be provided by experts in Sports Exercise and Health from Évora University, the study coordinator, and an available simulator controller from the Air Force team.

Upon the study’s conclusion, the waiting list group will be offered the same 12-week yoga classes before completing their tirocinium and departing the airbase, aligning with ethical considerations.

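### Pilots are allocated on inclusion, in a draw facilitated by their own team captain, and nothing places baseline testing before allocation, so baselines are open to arm-dependent bias

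*Protocol article*

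**What the plan says.** Section 3.2.2 ends with the briefing and signed consent. Section 3.2.3 follows: "Upon inclusion, volunteers will be allocated to either a waiting list (control group) or a yoga class (intervention group". The mechanism is given as "through a computer-based algorithm (random.org), to be facilitated by the team captain of the pilots".

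On who knows the result, section 3.2.3 says: "All study personnel, excluding the team captain and one study coordinator from Évora University, will be kept unaware of the group allocation". It adds: "Participants will be explicitly instructed to refrain from disclosing their group assignment to the study team". Pilots therefore know their arm at some point.

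Section 3.3.1 then describes baseline: "A baseline data collection session will be organized in Airbase 11 in Beja, with study participants selected randomly based on availability and location". The study coordinator is among those overseeing both the baseline and the post-intervention sessions, and the same section says that the coordinator leads the yoga classes. The Discussion (section 5) names the study coordinator as the one investigator who is not blinded.

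Sections 2.1 and 2.2 define every primary and secondary outcome as the 12-week value set against baseline. On class structure, section 3.2.1 says of the 19 pilots: "These pilots are divided into two classes". It describes the two classes as sharing aircraft and having comparable workloads and tasks.

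**The concern.** Unblinding after the intervention starts cannot be avoided in a yoga trial. Unblinding at baseline can be, because it depends only on whether pilots are measured before or after they are allocated.

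Many of the outcomes respond to effort or expectation: simulator task times and errors, handgrip, forced spirometry, and the SF-36, FFMQ, MAIA and ASAS questionnaires. A pilot who has just learned of a waiting-list place may try less. A pilot who expects to improve may rate the starting point lower. Either reaction alters the baseline for reasons unrelated to yoga, and the change score then carries it as if it were treatment effect. Operative performance, which section 2 calls the most crucial outcome for pilots' safety, is among the measures exposed.

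Two features add to this. The unblinded coordinator who will teach the classes helps to oversee the baseline session. The draw is also facilitated inside the pilots' own unit by someone who knows all the pilots and will know the allocation.

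A lesser issue is that 19 pilots in two classes can easily end up unevenly spread over the arms by chance.

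**Working it through.** **Order of events.** Placed side by side, the article gives consent (3.2.2), allocation on inclusion (3.2.3), baseline session for people already called study participants (3.3.1), then 12 weeks of yoga or waiting list. No sentence ties the baseline session to a time before allocation or before its disclosure. Allocation first is the natural reading, but it is an inference.

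**Who can know the arm at baseline if that order is followed.** The team captain and the coordinator (3.2.3), and the pilots once told. The coordinator is present at testing (3.3.1).

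**How a baseline shift enters the result.** Let each pilot's outcome be D = Y12 − Y0. Suppose knowledge of the arm moves mean baseline by s_Y in the yoga arm and s_W in the waiting-list arm.

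- Within the yoga arm, mean change moves by −s_Y.
- Between arms, the difference in mean change moves by −(s_Y − s_W).

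The transfer is one for one. The paired tests named in section 3.3.4 work on D within pilots, so they do not remove it. The documents give no figure for s_Y or s_W, and none is assumed here.

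**The plan's own figure.** The 19 in section 3.2.1 is a finite-population size for a frequency. With N = 19 and 95% confidence from the text, and p = 0.5 and d = 0.05 assumed because the image is not shown:

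n = N·p(1−p) / [(d²/z²)(N−1) + p(1−p)] = 4.75 / (0.0117 + 0.25) = 18.15, rounded up to 19.

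It reproduces, but it has no bearing on this point.

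**Chance imbalance by class (secondary).** Class sizes are not given; take 10 and 9. Fix the arms at 10 and 9 and ignore class. The number k of class-A pilots in the 10-pilot arm is hypergeometric, with C(19,10) = 92,378 equally likely draws. The difference in class share between arms is k/10 − (10−k)/9.

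- 30 points or more means k ≤ 3 or k ≥ 7: (10 + 405 + 4,320) + (10,080 + 1,620 + 90 + 1) = 16,526 draws, and 16,526 / 92,378 = 0.179.
- 20 points or more adds k = 4 (17,640 draws): 34,166 / 92,378 = 0.370.
- With assumed classes of 8/11 or 7/12, the chance of 30 points or more is 0.17.
- If the draw is balanced within class, the difference is fixed at about 4 to 7 points (0.056 for 9/10, 0.044 for 8/11, 0.067 for 7/12).

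**Chance imbalance in arm size, if the draw were simple 1:1 randomisation (assumed).** With X binomial(19, 0.5):

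- 7/12 or worse: 2 × 94,184 / 524,288 = 0.359.
- 6/13 or worse: 2 × 43,796 / 524,288 = 0.167.

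**The case against.** The strongest reply is that the article never says pilots know their arm when baseline is measured. Inclusion is not dated, the baseline section does not mention allocation, and the instruction not to disclose shows only that pilots know their arm at some point. That is correct. It limits the claim to what the stated order permits. It does not answer it, because no sentence places baseline first.

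A reader might infer that the captain can choose or repeat the draw. The text does not support this: a computer algorithm allocates and the captain facilitates. Details of concealment may also stand in a fuller protocol. With the whole population of 19 invited after a common briefing, there is little room to steer who enters. What stands is a structural weakness: the draw sits within the pilots' own chain of command.

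A reader might also infer that the two classes are different stages of training and that the allocation ignores them, so that simulator performance is confounded. The article does not describe the classes as stages, and calls their workloads and tasks comparable. Its silence on ratio and strata is what a condensed article commonly leaves out. Chance imbalance is also not bias, and a stable class difference cancels in change scores. The imbalance figures rest on assumed class sizes and an assumed type of draw, and they measure no effect on any outcome. Stratification is therefore an option, not a correction. Adjusting for class would need a between-arm model, which section 3.3.4 does not name.

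The Discussion already concedes the small sample and the difficulty of blinding pilots. It cites investigator blinding as mitigation, but the one exception is the person who oversees testing and teaches the intervention.

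**Conclusion.** The point holds on timing and on who handles the draw. Followed as written, the plan allows allocation to be known to the pilots and to the unblinded coordinator before baseline is measured. Any arm-dependent shift in effort or self-report then passes in full into every change score that depends on them. This rests on the natural reading of the section order and on the pilots being told their arm before testing, and the article states neither outright. The size of the bias cannot be derived from the documents.

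Class balance is a minor addition: an 18% chance of a gap of 30 points or more under assumed classes of 10 and 9 with a 10/9 draw. The documents do not support describing it as confounding.

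The change is worth making because it protects the baseline of every outcome at almost no cost.

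**What to change.** 1. In sections 3.2.3 and 3.3.1, state that baseline testing is completed for all pilots before allocation is generated or revealed to anyone, including the coordinator and the captain.
2. Have an existing Évora team member, outside the pilots' chain of command and with no testing or teaching role, make a single draw from coded IDs and release it to the captain only for scheduling. This needs no extra staff.
3. Optionally, make the draw balanced (10/9), ideally within class.
4. The abstract already describes the assignment in the past tense. If allocation has taken place, report the actual order of allocation and baseline testing, and who knew the allocation at baseline.

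The cost is that two steps change order and one short list is prepared.

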### Experimental procedure

3.3

#### Study flow

3.3.1

The study team will visit Airbase 5 in Monte Real to consult with the F16 Team Captain. The objectives include planning and scheduling visits, testing the proposed protocol, assessing all pertinent equipment, identifying, and rectifying potential errors before the initiation of the initial data collection. During this meeting, interviews with the Team Captain will be conducted to evaluate the perceived needs of pilots during their aircraft piloting duties. The insights obtained, combined with findings from the literature, will guide the tailoring of the yoga intervention.

A baseline data collection session will be organized in Airbase 11 in Beja, with study participants selected randomly based on availability and location undergoing evaluation over two consecutive days during pilots’ work hours from 8:30 to 19:00. Oversight of the data collection will be provided by experts in Sports Exercise and Health from Évora University, the study coordinator, and a simulator controller from the Air Force team.

The yoga group will integrate a one-hour yoga class into their work schedule, in Airbase 11 in Beja, twice a week for a 12-week period. For those on missions with conflicting schedules, alternative days and times will be accommodated. Each pilot is required to complete 24 yoga classes within the designated 12 weeks. The yoga intervention, led by the study coordinator—an Ashtanga Vinyasa Yoga expert with over 300 h of training and approximately 10 years of teaching experience—will be conducted.

Post-intervention data collection will follow the completion of the yoga program, with study participants, randomly divided based on availability and location, undergoing evaluation over two consecutive days, in Airbase 11 in Beja, during pilots’ work hours from 8:30 to 19:00. Supervision will be provided by experts in Sports Exercise and Health from Évora University, the study coordinator, and an available simulator controller from the Air Force team.

Upon the study’s conclusion, the waiting list group will be offered the same 12-week yoga classes before completing their tirocinium and departing the airbase, aligning with ethical considerations.

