## Discussion

5

Recognizing the critical role of cognitive performance in military operations, where impaired cognitive function is a prominent factor in accidents during training and combat (30), instructors must prioritize not only the physical health but also the psychological well-being of trainee pilots (31). The potential to enhance sensory systems, particularly through vestibular habituation and adaptation, can influence sensory weighting and postural behavior, the processing of sensations, along with their identification and integration with others, providing a comprehensive framework of possibilities for decision-making and action planning (32). Consistent yoga practice contributes to ongoing improvement in postural control, muscle strength, and the vestibular system, fostering increased plasticity in the sacculocolic pathway and resulting in enhanced vestibular evoked myogenic potential (cVEMP) responses (32). Furthermore, Ashtanga Yoga, in accordance with Patanjali, encompasses techniques that address all facets of the human system, including the body, breath, mind, personality, and emotions (11).

A notable strength of this intervention lies in its practicality and cost-effectiveness. Furthermore, all exercises are executable without the need for additional materials and can be conducted in spaces already designated for training, such as a gym room or outdoors when weather conditions permit.

The sample size may present challenges in interpreting results and deducing the practical relevance of the study. Challenges in maintaining blinding among pilots also present potential limitations. These are mitigated by including the totality of this population, designating the control group as a waiting list, offering them the same intervention subsequently, and ensuring blinding for all investigators except the study coordinator.

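### The unblinded study coordinator teaches the yoga and helps supervise the 12-week measurements, which weakens the investigator blinding offered as a mitigation

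*Protocol article*

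**What the plan says.** All places are in the protocol article.

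- **Randomization procedure and blinding (3.2.3), who knows the allocation:** "All study personnel, excluding the team captain and one study coordinator from Évora University, will be kept unaware of the group allocation".
- **Same section, processing and analysis:** "all data will be coded for subsequent processing and analysis, maintaining blindness to group allocation". The next sentence reads: "The final coded trial dataset will be made available to all team members for analysis". It makes no exception for the coordinator.
- **Recruitment and screening (3.2.2), delivery:** "a Ph.D. student will administer a yoga intervention at the chosen airbase 11 in Beja", while a university team collects the baseline and post-intervention data.
- **Study flow (3.3.1), delivery:** "The yoga intervention, led by the study coordinator". Each pilot in the yoga arm is to complete 24 one-hour classes.
- **Study flow, baseline session:** "Oversight of the data collection will be provided by experts in Sports Exercise and Health from Évora University, the study coordinator, and a simulator controller".
- **Study flow, post-intervention session:** "Supervision will be provided by experts in Sports Exercise and Health from Évora University, the study coordinator, and an available simulator controller".
- **Discussion (5):** the difficulty of blinding pilots is acknowledged as a limitation. Among the mitigations listed is "ensuring blinding for all investigators except the study coordinator".

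**The concern.** Pilots in a yoga versus waiting-list trial know their arm. The main remaining protection against biased measurement is that the people who run and score the tests do not. Exempting the instructor from blinding is unavoidable, and it does no harm if that person has no part in measurement or analysis. Here the exempted person is given a part in measurement and is not barred from analysis.

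By the 12-week session the coordinator has taught the yoga pilots for up to 24 hours each and knows them by sight. Asking pilots not to reveal their arm to the study team cannot conceal it from their own teacher.

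Some outcomes could respond to this. Operative performance, which the article calls the most crucial outcome for safety, includes a count and classification of emergency-protocol errors reported by the simulator controller. Handgrip and spirometry are read from instruments but depend on effort, and effort depends on encouragement. A supervisor with a stake in one arm could influence these, even without intending to, and the influence would tend to favour yoga.

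**Working it through.** No stated figure in the plan belongs to this point, so the check is mainly a side-by-side reading.

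**1. The coordinator's roles**

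| Role | Study coordinator | Source |
|---|---|---|
| Knows the allocation | Yes, by stated exemption | 3.2.3; Discussion |
| Teaches the yoga | Yes | 3.3.1 |
| Oversees the baseline session | Yes, shared | 3.3.1 |
| Supervises the 12-week session | Yes, shared | 3.3.1 |
| Receives the coded dataset | Not excluded | 3.2.3 |

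The fourth row conflicts with the purpose of the exemption. The Discussion is accurate that everyone but the coordinator is to be blinded. It does not mention that the exception is present, in a supervisory role, when outcomes are measured.

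**2. Which session is exposed**

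The 12-week session certainly is, because allocation is known and the classes have been taught by then. Exposure at baseline would require allocation to precede baseline testing. Section 3.2.3 places allocation at inclusion, which suggests this order but does not settle it.

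**3. Which outcomes are exposed**

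- *Open to judgement:* simulator error classification (primary, 2.1), reported by the controller in a session the coordinator helps supervise.
- *Open to encouragement:* handgrip and spirometry (secondary, 2.2).
- *Less exposed:* heart rate variability (chest monitor), centre of pressure (force plate) and body composition (impedance), all recorded by instruments.
- *Exposed whoever supervises:* questionnaires, because unblinded pilots complete them.

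**4. Who teaches**

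Section 3.2.2 names a Ph.D. student as the person delivering the yoga; 3.3.1 names the study coordinator. If they are the same person, the separation in 3.2.2 between the instructor and the data-collection team does not hold in 3.3.1. If they are two people, 3.2.3 omits an unblinded instructor from its exceptions. The text does not say which applies.

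**5. Illustration of size**

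The only input from the article is the total of 19 pilots. These are assumptions: a 10:9 split, no true effect, a spurious between-arm shift of d standard deviations, a two-sided 5% between-arm t-test and, for the adjusted case, a baseline correlation of 0.7.

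The noncentrality is d / √(1/10 + 1/9) = d / 0.4595. With baseline adjustment it is divided further by √(1 − 0.7²) = 0.714. Degrees of freedom are 17 unadjusted and 16 adjusted. The rejection probability is the area of the noncentral t beyond ±2.110 or ±2.120.

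| Assumed shift | Noncentrality, unadjusted | Rejection, unadjusted | Noncentrality, adjusted | Rejection, adjusted |
|---|---|---|---|---|
| 0.2 SD | 0.435 | 7.0% | 0.610 | about 9% |
| 0.3 SD | 0.653 | 9.5% | 0.914 | 13.8% |
| 0.5 SD | 1.088 | 17.7% | 1.524 | 29.9% |

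These rates do not describe the planned analysis. Section 3.3.4 specifies a paired t-test or a Wilcoxon test, not a between-arm comparison with or without adjustment. The table shows only that modest measurement bias could matter in a trial of this size.

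**The case against.** The strongest reply is that nothing is hidden. The exemption is stated in 3.2.3 and again in the Discussion, which claims blinding only for the other investigators. Supervision is shared with exercise experts and a simulator controller. No sentence says the coordinator scores, coaches or operates a test. Two of the three primary outcomes are instrument-recorded, and the judged one is reported by the controller, who should already be unaware of arm if counted as study personnel. Encouragement given equally to both arms would largely cancel in a between-arm comparison.

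Much of this stands, and it limits the point. A reader might infer that blinded assessment is defeated altogether. The text does not support that, because the other assessors are still meant to be blinded. Nor does it support three further inferences:

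- that baseline measurements are biased, since the order of allocation and baseline testing is not settled;
- that the coordinator devised the method, since the article identifies the coordinator as its teacher only;
- that the coordinator can decode the dataset, since the data are coded and the article does not say who holds the key. That detail may properly sit in the fuller documents. It remains true that with 19 pilots, coding may conceal little from someone who taught one arm and attended the measurements.

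The Ph.D.-student point is also conditional: on an ordinary reading, the student and the coordinator are one person.

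What the reply does not answer is why the one university person known to be unblinded needs to supervise the 12-week measurements at all. Disclosing the exemption does not remove that person's influence on the session.

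**Conclusion.** The concern holds in a limited form. As written, the unblinded yoga teacher helps supervise the post-intervention assessment and is not excluded from the analysis dataset. This undermines, but does not wholly defeat, the blinding that the Discussion relies on. The 12-week supervision conflict rests on the text alone. The points on baseline, the dataset and the identity of the instructor depend on facts the article does not give.

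The affected outcomes are chiefly simulator error classification, handgrip and spirometry. The size of any bias cannot be derived from the documents. The range of about 7% to 18% (unadjusted) or 9% to 30% (adjusted) is illustrative, resting on an assumed shift, split and correlation and on a test the plan does not use. The change is worth making because the safeguard matters in a trial where pilots cannot be blinded, and restoring it costs little.

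**What to change.** 1. In Study flow, take the study coordinator, and any other yoga instructor, out of supervising the 12-week measurements. Leave the session to the exercise experts and the simulator controller already named there, and state that they, including the controller who classifies errors, are kept unaware of arm.
2. In the blinding section, state that the coordinator takes no part in the analysis and does not receive the dataset until the primary analysis is locked.
3. Align Recruitment and screening, Randomization procedure and blinding, Study flow and the Discussion on who teaches, who is unblinded and who assesses. Say whether the Ph.D. student and the coordinator are the same person, and whether allocation comes before or after baseline testing.
4. If the coordinator cannot be separated from the session, state that outcome assessment is not fully blinded and remove investigator blinding from the mitigations in the Discussion.

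No additional staff or measurements are needed. The cost is a small scheduling inconvenience from having one fewer supervisor over the two assessment days.

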## Materials and equipment

2

Material and equipment selection for the study prioritized availability, capability to measure physiological functions impacted by piloting military aircraft, suitability for real-life training integration, and efficiency in delivering results without hindrance to pilots’ daily workload, as well as adherence to the highly specific military regulations in force.

Both primary and secondary outcomes were selected following a comprehensive review of the literature and a comparison with pilots’ perceived difficulties (as identified through a brief interview, detailed in the study flow). Primary outcomes were deemed the most critical factors in flights, with Operative Performance being the most crucial for pilots’ safety. Secondary outcomes were also identified as significant contributors.

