### Primary outcomes

2.1

Changes in Operative performance—Flight times to complete tasks in the flight simulator; number of errors during the emergency protocol and their classification report from the flight simulator controller (12). The assessment will determine if the exercise protocol influences the pilot’s decision-making, as evidenced by improved task efficiency, reduced errors, and enhanced visual and auditory reaction times (1, 2)—Time Frame: measured at 12 weeks (vs. baseline values).

Changes in Stress and HRV—Heart rate variability, measured with Polar H10 portable device (2, 13–15). The assessment will reveal if the exercise protocol influences pilots’ responses to stressors, with a lower stress response enhancing decision-making (4)—Time Frame: measured at 12 weeks (vs. baseline values).

Changes in Vestibular system control responses—The Center of Pressure (CoP) represents the dynamics of the neuromusculoskeletal system, was measured with a portable force plate (Biosignals Plux-Portugal) with a sample frequency at 1000 hz. and data downsampled to 100 Hz (16, 17). Preprocessing performed using the EEGLAB toolbox, which is available for use in MATLAB (The MathWorks Inc., Natick, MA) (18). Enhanced postural control responses may indicate the protocol’s potential to mitigate the effects of spatial disorientation (6, 7)—Time Frame: measured at 12 weeks (vs. baseline values).

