#### Statistical analysis

3.3.4

Sample size was calculated with OpenEpi. Data analyses will be done with MATLAB (18) and Jamovi (29), based on the type of data; analyses will be performed based on the underlying assumptions for parametric, or non-parametric testing. In detail, for all difference testing, data and variance distribution (i.e., normality) will be checked. The alpha-error threshold is set at 5%, all *p* values below are considered significant.

For the primary outcomes related with postural control and heart rate variability a MATLAB (18) routine will be used to treat data exported from the Biosignals Plux platform and also from the Polar H10 portable monitor, and with those values a Shapiro–Wilk normality test will be performed and either a T-test for paired samples will be applied on parametric data or a Wilcoxon rank test will be applied on non-parametric data.

For the primary outcomes related with operative performance and the secondary outcomes a Shapiro–Wilk normality test will be performed and either a T-test for paired samples will be applied on parametric data or a Wilcoxon rank test will be applied on non-parametric data.

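### Availability decides which simulator controller attends the 12-week session, and nothing ties that person to the baseline controller, although part of the leading primary outcome comes from the controller's report

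*Protocol article*

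**What the plan says.** Materials and equipment ranks the primary outcomes, with "Operative Performance being the most crucial for pilots’ safety". Primary outcomes (section 2.1) defines this outcome by simulator task times and by the "number of errors during the emergency protocol and their classification report from the flight simulator controller", assessed at 12 weeks against baseline.

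Study flow (section 3.3.1) lists who oversees each test session. At baseline these are the university's exercise experts, "the study coordinator, and a simulator controller from the Air Force team". At 12 weeks the experts and the coordinator appear again, but the third person becomes "an available simulator controller from the Air Force team". Each session runs over two consecutive days.

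Statistical analysis (section 3.3.4) names one approach for operative performance: a Shapiro–Wilk test, then a paired t-test or a Wilcoxon test. No comparison between the arms is named. Randomization procedure and blinding (section 3.2.3) keeps study personnel unaware of allocation, apart from the team captain and one coordinator.

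**The concern.** Counting and classifying errors in an emergency exercise depends in part on the judgement of the person reporting them. A change score built on such reports measures the pilot only if the rater, or at least the rater's standard, stays the same. Here the article states a basis for choosing the 12-week controller, namely availability, and that basis does not hold the rater constant. Blinding does not help: a controller who knows nothing of the allocation can still be stricter or more lenient than a predecessor.

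At stake is the reading of the outcome that the article itself puts first. If a more lenient controller attends at 12 weeks, all pilots appear to make fewer errors. Within the yoga arm that would look like the hoped-for gain in decision-making. If the controller's identity is not recorded, no later analysis can separate the two explanations.

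**Working it through.** **Inputs from the article.** 19 pilots; two arms; alpha 5%; paired tests of 12 weeks against baseline.

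**Assumptions.** Arms of 10 and 9 (the ratio is not stated); two-sided testing; normally distributed change scores; no true change. A new controller moves every score by s, in units of the SD of the change score. The article gives no rater variance, so s is shown as a range.

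**The plan's own figure.** The sample size of 19 can be reproduced with the finite-population formula n = N·p(1−p) / [(d²/z²)(N−1) + p(1−p)]. With N = 19, z = 1.96, and p = 0.5 and d = 5% assumed, n = 18.15, rounded up to 19. It sets a frequency in a finite population and does not bear on rater change; only the total of 19 is used below.

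**Paired test within one arm.** With no true change and a rater shift s, the t statistic follows a noncentral t distribution with n−1 degrees of freedom and noncentrality s·√n. The false-positive rate is P(|T| > t(0.975, n−1)). For n = 10 and s = 0.5, the noncentrality is 0.5 × √10 = 1.58 and the rate is 29.3%. For n = 9 it is 0.5 × √9 = 1.5 and the rate is 26.3%.

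| Shift s | Paired, n = 10 | Paired, n = 9 | Yoga significant, control not | Between arms, common shift |
|---|---|---|---|---|
| 0 | 5% | 5% | 4.8% | 5.0% |
| 0.25 | 10.9% | 10.2% | 9.7% | 5.0% |
| 0.5 | 29.3% | 26.3% | 21.7% | 4.9% |
| 0.75 | 56.2% | 50.7% | 27.6% | 4.9% |
| 1.0 | 80.3% | 74.8% | 20.0% | 5.0% |

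The last two columns come from 100,000 simulated trials of 10 against 9. The fourth column is the pattern most easily read as a yoga effect when each arm is tested on its own.

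**Why the between-arm column stays at 5%.** If one controller scores both arms at 12 weeks, the expected difference in mean change is (yoga change + s) − (control change + s), and s drops out.

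**The case against.** The strongest reply is that one adjective carries the point. The Study flow sentences describe staffing, not scoring, and section 2.1 speaks of the controller in the singular. A condensed article need not say that the same rater scores both visits. Part of this stands: the article does not say that the controller will change, and a reader who infers that it will goes beyond the text. But the article is not merely silent. It describes the other supervisors alike at both visits and gives availability as the basis for the controller at 12 weeks only.

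A reader might also infer a bias between the arms, with two controllers sharing the two test days and seeing different mixes of pilots. The documents do not support this. Each sentence names one controller per session; it is the pilots who are "randomly divided based on availability and location, undergoing evaluation over two consecutive days". Even if two controllers split the 19 pilots about equally, the between-arm difference in the share seen by one of them would have an SD of √(0.25 × (1/10 + 1/9) × 19/18) = 0.236. That is chance imbalance centred on zero, not a directional bias. With a strictness gap of 1 SD of the error score it adds noise of about 0.24 SD, against ordinary sampling error of √(1/10 + 1/9) = 0.46 SD. With a deliberately uneven split, 7 of 10 against 3 of 9, the bias is (0.70 − 0.33) × s = 0.37s, and the false-positive rate of a between-arm test is 5.3% to 8.1% for s from 0.25 to 1.0.

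Finally, the large within-arm rates arise because only paired tests are named, and training or repeat exposure could also move paired scores. That is right, and it is why the fix includes a between-arm comparison. It does not remove the case for holding the rater constant. The blinding rule may already cover the controller, but the article does not say whether Air Force staff count as study personnel.

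**Conclusion.** The point holds as a weakness in how the measurement is fixed, not as a demonstrated bias. Availability decides who attends at 12 weeks, that person is not tied to the baseline controller, and the paired tests would take any difference in strictness as change in the pilots. If the controller changes and the assumed shift is 0.25, 0.5 or 1.0 SD of the change score, the per-arm false-positive rate is about 10-11%, 26-29% or 75-80%. If the same person scores both visits to the same standard, it is 5%.

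The figures rest on the assumed shift, arms of 10 and 9, and normal change scores. They apply to the controller-reported errors only; the article does not say whether task times also depend on the controller. Bias between the arms would need more than one controller in a session, spread unevenly over the arms, which the text does not state.

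**What to change.** In Study flow, replace "an available simulator controller from the Air Force team" with a rule to this effect: the same simulator controller, unaware of allocation, scores the same emergency scenario for all pilots at both visits.

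If duties prevent this, each pilot keeps the same controller at both visits, and the coordinator who already knows the allocation balances controllers across the arms. This fallback has to be arranged before baseline, because the pairing of pilot and controller starts there.

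In either case, record the controller's identity code with each score. In Statistical analysis, compare the change in errors between the arms, so that any remaining shift common to both cancels.

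The cost is a rostering request for the two two-day sessions, with no extra assessor. The downside is that test dates then depend on a controller's roster, which may be hard to arrange under the military constraints that the article describes. The fallback eases this but requires the unblinded coordinator to plan the sessions.
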